##### Macro-level: social support

Parent social support is measured using the abbreviated version of the Interpersonal Social Support Evaluation List (ISEL-12 [96]). The ISEL-12 is a 12-item questionnaire comprising three subscales: appraisal support (availability of someone to talk to about problems), belonging support (availability of someone to do things together with) and tangible support (availability of someone to help with practical matters). We will use the total score for our main analysis (research question 4). Items describe statements (e.g., ‘I feel that there is no one I can share my most private worries and fears with’), which the participant rates for agreement on a four-point scale ranging from ‘Definitely false’ (1) to ‘Definitely true’ (4). ISEL-12 total scores range from 12 to 48, and will be coded in such a way that higher scores indicate more support. The ISEL-12 total score has good psychometric properties, with adequate to good internal consistency, adequate test-retest reliability, and good construct validity [96, 97]. We translated the ISEL-12 to Dutch using the back-translation method. We also added two self-made items reflecting aspects of social support we were interested in in light of our intervention: ‘There is someone who could look after my child(ren) for a day if I were not doing well’ (tangible support) and ‘If I were worried about the impact of my problems on my child, there would be someone I could talk to about it’ (appraisal support). These will be analyzed descriptively.

##### Macro-level: parenting stress

Parenting stress is measured using parent-report on an abbreviated Dutch version of the Parenting Stress Index (PSI [98, 99]). This abbreviated version is a 25-item questionnaire measuring stress related to childrearing and the parental role. Items are statements (e.g. ‘There are some things my child does that really bother me a lot’) which parents rate for agreement using a 6-point Likert scale ranging from ‘Totally disagree’ (1) to ‘Totally agree’ (6). We will use the total score as our analysis outcome (research question 5). The Dutch version of the PSI has acceptable validity [99].

##### Macro-level: child overall psychological problems

Child overall psychological problems are measured using parent-report on the Dutch translation of the Strengths and Difficulties Questionnaire-Parent Report (SDQ-P [100, 101]). The SDQ-P is a 25-item questionnaire suitable for parent-report on emotional and behavioral symptoms of children aged 4–17. The SDQ-P comprises five subscales with five items each: hyperactivity/attention deficit, emotional problems, behavioral problems, peer relationship problems, and prosocial behavior. SDQ-P items describe characteristics or behaviors (e.g., ‘Many worries, often seems worried’), for which parents rate to which extent these are true for their index child on a three-point Likert scale ranging from ‘Not true’ (0) to ‘Certainly true’ (2). We will use the ‘general difficulties’ score as our analysis outcome (research question 6), which aggregates all subscales excluding prosocial behavior (thus comprising 20 items). We will perform additional analyses on the separate subscales. The ‘general difficulties’ score ranges from 0 to 40. The SDQ-P has good psychometric properties, with adequate internal consistency and test-retest reliability and good construct validity [102].

##### Macro-level: child PTSD symptoms

Child PTSD symptoms are measured using parent-report on the Dutch translation of the Child and Adolescent Trauma Screener-Caregiver Report (CATS-C [103, 104]). The CATS-C has two versions; one for children aged 3–6 and one for children aged 7–17. Both versions start with 15 yes/no items about child exposure to DSM-5 A-criterion traumatic events (e.g., ‘Serious natural disaster like a flood, tornado, hurricane, earthquake, or fire’). We have added one item (‘Learning from me or someone else about the traumatic experience(s) I have had’), because this potentially traumatic experience was not included in the original questionnaire. Furthermore, we have added an item to assess whether the parent and child were co-exposed to the same trauma (e.g., being in an accident together, shared exposure to domestic violence). This item states: ‘Was your child present during a traumatic event you experienced? For example, did you experience it together, or did your child witness it happening to you?’

If the parent reports their child has been exposed to at least one traumatic event, the questionnaire continues with 16 (age 3–6) or 20 (age 7–17) items about PTSD symptoms (e.g., ‘Being overly alert or on guard’). Data on PTSD symptoms are thus only collected if the child has experienced at least one A-criterion traumatic event. PTSD symptom items are rated for frequency in the past two weeks on a four-point Likert scale ranging from ‘Never’ (0) to ‘Almost always’ (3). The CATS-C also contains five yes/no items about interference with life domains (e.g., ‘Getting along with others’). The PTSD symptom items are divided into four subscales corresponding with DSM-5 PTSD symptom clusters. Total symptom scores range from 0 to 48 (age 3–6) or 0–60 (age 7–17). In this study, we use the total symptom scores as our analysis outcome (research question 7). We will perform additional analyses on the separate subscales. Scores on trauma exposure items will be reported descriptively. The PTSD symptom measure of the CATS-C has good psychometric properties, with good to excellent internal consistency and good construct validity [103]. As of yet, test-retest reliability has only been assessed for the self-report version of the CATS, which shows adequate test-retest reliability [105].

### Background and moderator variables

#### Macro-level: trauma type/timing

Lifetime trauma exposure will be measured at pretest using the Dutch translation of the Life Events Questionnaire for DSM-5 (LEC-5 [106, 107]). The LEC-5 comprises 17 items which describe DSM-5 A-criterion traumatic events (e.g., ‘Fire or explosion’). Participants note for each event on a scale with six options whether they were directly or indirectly (i.e., as a witness, learning about it happening to someone close to them, or as part of their job) exposed to it. In case of multiple trauma exposures, the participant is asked to indicate which event bothers them the most (the ‘index trauma’). Psychometric properties for the LEC-5 have not yet been established, but the highly similar previous version (LEC-IV) has good psychometric properties, with adequate test-retest reliability and good construct validity [108].

#### Macro-level: PTSD symptoms

PTSD symptoms will be measured at pretest using the Dutch translation of the PTSD Checklist for DSM-5 (PCL-5 [107, 109]). The PCL-5 comprises 20 items describing PTSD symptoms in relation to the index trauma (e.g., ‘Becoming upset when something reminded you of the stressful experience’), which are rated for past-month frequency on a five-point Likert scale ranging from ‘Not at all’ (0) to ‘Extremely’ (4). The PCL-5 comprises four subscales corresponding to DSM-5 PTSD symptom clusters (intrusion, avoidance, negative alterations in mood and cognitions, and hyperarousal). We will use the PCL-5 total score as a moderator variable (research question 8). PCL-5 total scores range from 0 to 80. The PCL-5 has good to excellent psychometric properties, with excellent internal consistency, good test-retest reliability and good construct validity [109].

#### Macro-level: psychosocial functioning

Among the most common comorbid disorders with PTSD are major depressive disorder, anxiety disorders and substance abuse disorders. Problems in life domains such as relationships and professional functioning are also common in PTSD [83]. We therefore report descriptively on general psychosocial functioning in the sample. This is measured as part of routine outcome monitoring at Arkin Mental Health Care using the Outcome Questionnaire-45 (OQ-45 [110]). We will use the closest measurement before pretest. The OQ-45 is a commonly used questionnaire for measuring clinical outcomes. It comprises 45 items, which are divided into three subscales: symptom distress (25 items, measures symptoms of depression, anxiety and substance abuse), interpersonal relations (11 items, measures relational functioning) and social role (9 items, measures functioning in school, work and/or leisure). Items describe symptoms/situations (e.g., ‘I feel no interest in things’), which participants rate for past-week frequency on a 5-point Likert scale ranging from ‘Never’ (0) to ‘Always’ (4). We will report the OQ-45 total score, which ranges from 0 to 180, and subscale scores, which range from 0 to 100 (symptom distress), 0–44 (interpersonal relations), and 0–36 (social role). The OQ-45 has good psychometric properties, with good test-retest reliability, adequate to excellent internal consistency, and good construct validity [110].

#### Macro-level: demographic information

To provide information on the demographic background of the sample, participants complete a short demographic questionnaire (DQ) at pretest with items about characteristics such as age, gender, employment status, family composition, and number of children.

#### Macro-level: intervention adherence and satisfaction

For participants in the intervention condition, intervention adherence (completion of online modules; attendance of in-person sessions; and use of PTSD-specific content in the online library) will be reported descriptively. Furthermore, these participants complete a short satisfaction questionnaire (SQ) at posttest. The SQ contains closed-ended and open-ended questions on aspects of the intervention, and invites participants to provide suggestions for improvement. Results will be reported descriptively in the publication of the current study and will be used for future improvement of the intervention.

#### Micro-level: parental PTSD symptoms

PTSD symptoms are assessed using EMA with an abbreviated version of the PTSD Checklist for DSM-5 (PCL-5-A). This version contains the 10 PCL-5 items with the strongest factor loading for their respective symptom cluster. It was created for and used successfully in previous EMA research [111, 112]. The PCL-5-A contains three items for intrusion, two for avoidance, two for negative cognitions and mood, and three for hyperarousal. Participants are asked to report on their symptoms during the current part of the day using the same five-point Likert scale as in the regular PCL-5 (‘Not at all (0) to Extremely (4). Total scores range from 0 to 40.

#### Micro-level: sleep quality

Sleep quality is assessed in the first EMA assessment of each day, using a single item (‘Last night, how would you rate your sleep quality overall?’) from the Pittsburgh Sleep Quality Index [113]. Sleep quality is rated from ‘Very good’ (0) to ‘Very bad’ (3). The normal instruction is ‘During the last month’; this is replaced with ‘Last night’ to fit the EMA format. This adaptation has been used successfully in previous EMA research [111].

#### Micro-level: situational context

To assess the situational context, each EMA questionnaire starts with two situation items (Where are you?; What are you doing?), answered using multiple choice.

### Data management

Data management is carried out according to a protocol to ensure security and quality. This data management protocol can be found on our Open Science Framework page [114].

### Safety reporting and monitoring

Research team members involved in assessments and contact with participants and prevention professionals carrying out the intervention sessions are instructed in the reporting procedure of (serious) adverse events. These must be reported to the primary investigator according to guidelines by the Central Committee for Research in Humans [115]. Engaging a data monitoring committee or auditor and performing interim analyses is considered not to be necessary due to the low-risk nature of the study.

### Analysis

Primary analyses will be conducted on the entire randomized sample (i.e., intention to treat). Extra analyses for comparison will be conducted on the per protocol/treatment completers sample. Participants in the intervention condition who have completed at least six out of eight intervention modules/sessions will be characterized as treatment completers. Participants who fail to complete the intervention, but do not choose to drop out of the study, will complete the posttest and follow-up assessments as normal. Hypothesis testing will be two-sided with an alpha level of .05. Missing data will be handled using multiple imputation (R package MICE or equivalent).

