### Aims of this study

#### Primary objective

To test the effect of KopOpOuders-PTSD on macro- and micro-level parenting behavior by answering the following research questions:What is the effect of KopOpOuders-PTSD on macro-level parenting behavior?

H1. We hypothesize that parenting behavior at posttest will be more adaptive in the intervention condition than in the control condition. This effect is hypothesized to remain stable at follow-up.2.What is the effect of KopOpOuders-PTSD on micro-level parenting behavior?

H2. We hypothesize that micro-level parenting behavior will be significantly more adaptive at posttest in the intervention condition than in the control condition.

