### Participants

#### Sample size

We assumed a medium effect size for the primary macro-level outcome (parenting behavior: Alabama Parenting Questionnaire), *d* = 0.55, based on RCTs with similar designs, interventions and populations as the current study, and with the same primary outcome [21, 82]. With a power of 0.80 and significance level of *p* = .05, the minimum *n* is 53 per condition. From previous experience with intervention studies in adults with PTSD, we expect 20–25% dropout. We therefore corrected with 25% oversampling, resulting in 53/0.75 = *n* = 71 per condition, total *N* = 142.

For the primary micro-level outcome (parenting behavior: Short Parenting Scale for EMA), power was calculated using PowerAnalysisIL [83] using our best estimation of relevant parameters. Based on existing EMA literature [84], we assume participants will respond to 70% of the 42 EMA prompts, resulting in 29 complete data points per participant. Assuming an autocorrelation between measurement occasions of *r =* 0.30 and a medium effect size, minimum sufficient power to detect intervention effects would be reached if *n =* 32 (16 per condition) agreed to take part in the EMA component of the study.

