### Instruments

#### Primary outcomes

##### Macro-level: parenting behavior

Parenting behavior is measured using the Dutch translation of the caregiver-reported Alabama Parenting Questionnaire (APQ [86, 87]). The APQ is a 42-item questionnaire with five subscales: positive involvement with children, supervision/monitoring, use of positive discipline techniques, consistency in discipline techniques, and use of corporal punishment. Items describe parenting behaviors and situations (e.g., ‘You don’t tell your child where you are going’), which are scored for frequency on a five-point Likert scale ranging from ‘never’ (1) to ‘always’ (5). APQ total scores range from 42 to 210. However, subscales are often analyzed separately, with higher scores reflecting higher parenting skills on the ‘positive involvement’ and ‘positive discipline techniques’ subscales, and lower parenting skills on the other three subscales. In this study, we will use the total score as the primary outcome for the main analysis (research question 1) and perform additional analyses on the separate subscales. The APQ has good psychometric properties, with adequate to good internal consistency [88, 89] good test-retest reliability [90] and good construct validity [88, 89].

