### Dissemination policy

The results of this study will be submitted for publication in an international peer-reviewed open access journal. The principal investigator will determine publication strategy. Results will also be communicated to the public through online newsletters. KopOpOuders-PTSD will be made available to other institutions within the Netherlands if it is found to be effective in this study. The online modules can be obtained under license from Trimbos Institute; the protocol for the face-to-face sessions will be made freely available to institutions when they acquire this license. A process evaluation report will be published to inform other professionals about the implementation process, potential challenges and solutions. Institutions wanting to implement KopOpOuders-PTSD can refer to this process evaluation report for implementation advice.

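### Two primary outcomes are each tested at two-sided .05 with no stated order or combination rule; if either may count, the chance of a false-positive primary result is about 9 to 10%

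*Protocol article*

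**What the plan says.** The primary objective in the Protocol article covers two levels of measurement: "To test the effect of KopOpOuders-PTSD on macro- and micro-level parenting behavior". Each level has its own hypothesis at posttest. For the macro level it reads "We hypothesize that parenting behavior at posttest will be more adaptive in the intervention condition than in the control condition", and for the micro level "We hypothesize that micro-level parenting behavior will be significantly more adaptive at posttest in the intervention condition than in the control condition". H1 adds an expectation that the effect persists at follow-up.

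Both measures are described under Instruments, Primary outcomes. The Sample size section gives each its own power calculation, the second introduced by "For the primary micro-level outcome (parenting behavior: Short Parenting Scale for EMA), power was calculated using PowerAnalysisIL". Each also has its own model (Macro-level: primary and secondary outcomes; Micro-level: primary endpoint).

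The Analysis section sets one level for everything: "Hypothesis testing will be two-sided with an alpha level of .05". Nowhere does the article say how the two primary results are to be ordered or combined.

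The Dissemination policy attaches a consequence to the result, without naming the outcome that decides it: "KopOpOuders-PTSD will be made available to other institutions within the Netherlands if it is found to be effective in this study".

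**The concern.** With two outcomes labelled primary, each carrying the full .05, the reader cannot tell what a positive trial is. The text fits three rules: either outcome suffices, both are required, or the APQ leads and the EMA measure supports it. Under the first rule the error rate for a primary claim is above the level stated for each test.

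The two outcomes also differ in weight. The APQ total sets N = 142. The SPS-EMA total comes only from participants who opt in to EMA (Micro-level assessments), and the Sample size section regards 32 of them, 16 per condition, as sufficient. Without a stated order, a significant result in that subset could be presented as a positive primary outcome, and cited in support of roll-out, although the outcome for which the trial was sized shows nothing.

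**Working it through.** **Inputs from the Protocol article.** d = 0.55, power 0.80, alpha .05, 53 per condition, 25% dropout, 71 per condition, N = 142 (Sample size); 1:1 allocation (Study design); two-sided .05 (Analysis); EMA optional (Micro-level assessments); 32 EMA participants as the minimum (Sample size). The correlation between the two test statistics is not given, so it is assumed over a range.

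**1. The plan's own sample size.** For two means, the normal approximation is n = 2(1.960 + 0.842)² / 0.55² = 15.70 / 0.3025 = 51.9, so 52 per condition. The t-based solution is 52.87, so 53, as stated. Then 53 / 0.75 = 70.7, so 71 per condition and N = 142. A one-sided .05 would give only about 42. The APQ comparison therefore uses the whole two-sided .05, and nothing is set aside for a second primary.

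**2. At least one false-positive primary, if either may count.**
- Independent tests: 1 − 0.95² = 0.0975.
- Correlated tests: 1 − P(|Z₁| < 1.96 and |Z₂| < 1.96), bivariate normal with correlation r.

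| r (assumed) | Either direction | In favour of the intervention |
|---|---|---|
| 0 | 0.0975 | 0.0494 |
| 0.3 | 0.0951 | 0.0476 |
| 0.5 | 0.0907 | 0.0454 |
| 0.8 | 0.0781 | 0.0390 |

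The right-hand column uses 0.025 per test, the favourable half of a two-sided .05. With independence it is 1 − 0.975² = 0.0494, to be compared with 0.025 for one test.

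**3. Which r is plausible.** Only part of the sample contributes to both tests, so the correlation between the test statistics is roughly the outcome correlation times √(n_EMA / 142). For an assumed outcome correlation of 0.5:
- 32 EMA participants: 0.5 × √(32/142) = 0.24, error 0.096.
- All 142: r = 0.50, error 0.091.

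**4. What each remedy costs.**
- Equal split, .025 each: 64.1, so 65 evaluable per condition; 65 / 0.75 = 86.7, so 87 per condition and N = 174. At the planned 53 evaluable, APQ power falls from 0.80 to 0.71.
- Fixed sequence, APQ first: if the APQ null is true, no false primary claim can arise unless the APQ test rejects, which has probability .05. If the APQ effect is real, the only possible false claim is on the SPS-EMA, again at .05. The familywise error stays at .05, and 53 and 71 per condition stand.
- Both must succeed: no inflation, but joint power would be below 0.80.

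**The case against.** The strongest objection is that testing order is typical SAP content, that an SAP may exist, and that the blanket .05 sentence is not itself wrong, since it fits a fixed sequence or a both-must-succeed rule equally well. It is true that an unseen SAP could contain a rule. But this article is not silent on the matter. It fixes the level, names two primaries, spends the full .05 on the APQ and links a consequence to the result. Which outcome decides belongs with those statements.

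A second objection is that the inflation depends on an either-may-count reading. This stands, and the conclusion below is conditional on it. The article poses two separate questions, and reporting each answer on its own is a possible intention. The Measurement levels section describes EMA as a supplement to the questionnaires, which suggests that the APQ leads. That supports stating the order rather than leaving it to be inferred.

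Two stronger readings are tempting and not supported:
- A reader might infer that the error of the roll-out decision exceeds .05. For the two posttest primaries it does not. Roll-out needs a result in favour of the intervention, and that false-positive chance is at most about 4.9%. It is close to double the 2.5% of a single test, but still below .05.
- A reader might count the APQ follow-up contrast as a third chance and compute 1 − 0.95³ = 14.3%. H1 treats follow-up as persistence of a posttest effect, not as a separate route to success. Posttest and follow-up scores also come from the same participants, instrument and model, so they cannot be taken as independent.

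Nor is the EMA comparison unrandomized. Participants agree to EMA before allocation (Inclusion, pretest, and randomization). The issue is how far a self-selected subset represents the trial, and which test decides.

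**Conclusion.** The point holds as a gap in the decision rule; the sample size arithmetic is correct. If success on either primary may be claimed, the chance of at least one false-positive primary is about 9.1 to 9.75% for test correlations from 0.5 down to 0, and about 7.8% at 0.8. In favour of the intervention it is about 4.5 to 4.9% over the range 0.5 to 0, against 2.5% for one test. These figures rest on the either-may-count reading, which the article leaves open, and on assumed correlations. Under a both-must-succeed rule or an APQ-first sequence there would be no inflation, but neither is stated. The practical risk is a primary claim resting on the optional EMA subset when the APQ is null. The point should be settled before the data are analysed, and it does not call the design into question.

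**What to change.** Add one paragraph to the Analysis section:

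1. APQ total at posttest is tested first, at two-sided .05.
2. SPS-EMA total at posttest is tested as confirmatory, at two-sided .05, only if the APQ result is significant. Otherwise its estimate and 95% CI are reported as supportive.
3. The APQ follow-up contrast is supportive evidence of persistence.

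In the Dissemination policy, state that effectiveness refers to the APQ result at posttest. If an SAP already contains a rule, state that rule in the protocol.

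The change leaves N = 142 and the APQ power of 0.80 as they are. Its cost is that an SPS-EMA effect cannot be claimed as confirmatory when the APQ is null. This is a real cost, because the Measurement levels section justifies EMA partly by possible memory bias in retrospective reports. Sponsors who give that argument more weight could split alpha instead. An equal split needs N = 174, or accepts APQ power of about 0.71 at the planned 53 evaluable per condition.
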